**Fig. 4 Fig4:**
[figure not shown]
Flowchart. * Questionnaires: Menstruation questionnaire, SF-36 (Short Form-36 [29, 30]), Euro-Qol 5D [31], FSFI (Female Sexual Function Index) [32], menstruation chart [28], costs and consultation diary, HLQ (Health and Labour Questionnaire) [33]

### Intervention (hysteroscopic niche resection)

The patients allocated for hysteroscopic niche resection will undergo the procedure under spinal or general anaesthesia in ambulatory setting. After dilatation of the cervical os up to Hegar 9 mm, the hysteroscopic resection will be performed using a 9 mm resectoscope in a standardized way, as described below. In case of bipolar currency, 0.9 % NaCL and in case of monopolar currency, sorbitol fluid will be used to induce distension of the uterine cavity. The niche will be evaluated by hysteroscopy and standardized characteristics will be registered (Fig. 5).

**Fig. 5 Fig5:**
[figure not shown]
Schematic diagram of niche characteristics during hysteroscopy

The bladder will be filled with methylene blue solution during the procedure to enable early identification of eventual bladder injuries. The procedure will be performed under continuous combined sonographic evaluation to ensure sufficient distance between the resection and coagulation area and the bladder. The distal rim of the niche in utero, if prominent visible, will be resected (Fig. 6) as described by i.a. Chang et al. and Fabres et al. and the niche surface will be superficially coagulated. Eventual polyps in the niche will be resected. A maximum fluid loss of 1000 ml Sorbitol or 2000 ml NaCl is accepted. Surgical outcomes such as satisfaction of the gynaecologist, surgical steps, complications and postoperative hospital stay will be registered in the case report file. Name and experience in numbers of resections of the gynaecologist with hysteroscopic niche resections will be registered. All gynaecologists will be evaluated in performing the resection using an Objective Structured Assessment of Technical Skills (OSATS). In case of an uneventful procedure, patients will be discharged on the same day.

**Fig. 6 Fig6:**
[figure not shown]
Resection of the distal part of the niche. Is a modified figure of the one that was published by Gubbini et al. 2008 [18] and v.d. Voet et al. [26]

### Control group (expectant management)

The control group will receive no additional intervention during the first six months after randomisation. Patients will be encouraged to continue the medication and/or oral contraceptives during this period as used before randomisation. Six months after randomisation all types of additional therapies are allowed. All additional therapies given up to six months will be registered in both the intervention and the control group, such as oral contraceptives, IUD placement or hysterectomy.

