### Outcome measures

The primary outcome is the number of days with postmenstrual spotting during one menstrual cycle 6 months after randomisation.

Secondary outcomes are the menstrual characteristics, menstrual related pain and experienced discomfort of both spotting and menstrual pain on VAS of 0–10), quality of life (SF-36, EuroQoL5D, patient satisfaction (5 point scale), sexual function (FSFI), micturition frequency, and urinary incontinence, absence from work (HLQ: Health and Labour [33]), medical consultation, medication use and received additional therapies (diary) at 3 and 6 months after randomisation.

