#### Statistical analysis

Analyses will be performed according to intention-to-treat principle and additionally by per protocol analysis. All tests will be performed two sided and a *p*-value <0.05 will be considered as statistically significant. The difference between the two groups at 6 months follow-up regarding total number of postmenstrual spotting days during one menstrual cycle, duration of menstrual bleeding, number of days of brownish discharge, menstrual pain, experienced discomfort of spotting and of menstrual pain, SF-36 domain scores and EuroQol will be analysed using linear regression analyses, adjusted for relevant baseline values. Potentially relevant confounders are additional hormonal therapy, smoking and use of anticoagulation. Logistic regression analysis will be used to evaluate the existence of (midcycle) intra-uterine fluid. To compare satisfaction with treatment, reported on a 0–5 point scale at six months a (multinominal) logistic regression analysis will be used.

We have planned four subgroup analyses, for:

1) Total days of spotting at the end of the menstruation and intermenstrual spotting >25^th^ centile versus ≤ 25^th^ centile and >75^th^ centile or ≤75^th^ centile at baseline;

2) Number of days postmenstrual spotting >25^th^ centile versus ≤2 25^th^ centile and >75^th^ centile versus ≤75^th^ centile at baseline;

3) Small versus larger niches (using a cut-off of residual myometrium of 3 and 5 mm and <50 % of total myometrial thickness (sum of RM and niche depth) at baseline;

4) A history of 1 versus more than 1 CS at baseline.

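### The Statistical analysis section lists additional hormonal therapy, which can follow from allocation, as a potential confounder of the randomised comparison

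*Protocol article*

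**What the plan says.** In the Protocol article, Statistical analysis, the month-6 outcomes, including postmenstrual spotting days, are compared by linear regression with adjustment for baseline values. The populations are given as "Analyses will be performed according to intention-to-treat principle and additionally by per protocol analysis". The next statement on covariates is "Potentially relevant confounders are additional hormonal therapy, smoking and use of anticoagulation".

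Three other sections bear on what additional therapy means:

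- Control group (expectant management): "The control group will receive no additional intervention during the first six months after randomisation". Patients are encouraged to stay on the medication or contraceptives they used before randomisation. Then: "All additional therapies given up to six months will be registered in both the intervention and the control group". The examples given are oral contraceptives, IUD placement and hysterectomy.
- Outcome measures: the secondary outcomes include "medical consultation, medication use and received additional therapies (diary) at 3 and 6 months after randomisation".
- Economic evaluation: the authors hypothesise that resection lowers spotting and, with it, consultations, therapies applied and sick leave.

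**The concern.** A confounder of a treatment comparison must be a cause, or stand in for a cause, of who receives the treatment. In a randomised trial, nothing that starts after randomisation can play that role. A therapy started because spotting persisted lies downstream of allocation. Putting it in the regression compares arms within groups defined by early response, and response depends on the arm and on the patient's own prognosis. That can create a difference where none exists or shrink one that does.

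The women know their allocation and report the outcome themselves (Strengths and limitations), so the decision to start add-on therapy may also depend on arm directly. At stake is the adjusted estimate of the primary outcome. If that covariate enters the primary model, the estimate is no longer the intention-to-treat effect that the same section announces.

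**Working it through.** **Which reading the text supports.** The control-group section has two categories: what was used before randomisation and is continued, and additional therapies given up to month 6. Its examples of the second include hormonal treatments. Outcome measures then counts received additional therapies as a result of the trial, and Economic evaluation expects the arm to change the therapies applied. The same variable cannot be both a possible effect of allocation and a confounder of it.

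**The plan's own figure.** The sample size is not in dispute. With a difference of 2 days, SD 2.7, two-sided 5% and 90% power, the t-test needs 39.3, so 40 per arm, and 40/0.8 = 50, as stated.

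**Inputs for an illustration.** From Sample size: SD 2.7, baseline mean 7.5, relevant difference 2 days. Assumed, because the documents do not give them: normal spotting counts with common correlation r between baseline, month 3 and month 6; therapy T starts when month-3 spotting exceeds a cut-off; T lowers month-6 spotting by d days (0 or 2). The models are month-6 spotting on arm and baseline, without and with T, with 600,000 simulated women per arm. Positive values favour resection.

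*Scenario A: no true effect; the 10% of resected women with most month-3 spotting start therapy, no controls do.*

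| d | without T | with T, r = 0 / 0.3 / 0.5 / 0.7 |
|---|---|---|
| 0 | 0.00 | 0.00 / 0.11 / 0.14 / 0.12 |
| 2 | 0.20 | 0.00 / 0.11 / 0.14 / 0.12 |

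Hand check of the right column: leaving out the top 10% lowers the month-3 mean of the rest by 2.7 × φ(1.2816)/0.9 = 2.7 × 0.1755/0.9 = 0.527 day. Of this, about r(1 − r) carries over to month 6 after adjustment for baseline: 0.21 × 0.527 = 0.11 at r = 0.3 and 0.7, and 0.25 × 0.527 = 0.13 at r = 0.5. The 0.20 is 10% × 2 days.

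With 40 women per arm and d = 0, the two-sided false-positive rate at r = 0.3 to 0.7 is 5.4–6.0% with T and 4.6–5.3% without (simulation error about 0.25 points).

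*Scenario B: true effect 2 days; the same cut-off in both arms.*

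| controls / resected starting therapy | d | without T | with T, r = 0.3 to 0.7 |
|---|---|---|---|
| 10% / 2% | 0 | 2.00 | 1.89–1.91 |
| 40% / 16% | 0 | 2.00 | 1.68–1.76 |
| 40% / 16% | 2 | 1.52 | 1.68–1.76 |

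The resected shares follow from the shift 2/2.7 = 0.741 SD: 1 − Φ(1.282 + 0.741) = 2% and 1 − Φ(0.253 + 0.741) = 16%. The 1.52 is 2 − 2 × (0.40 − 0.16).

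With inert therapy, adjustment costs 0.09–0.11 day at 10% control uptake and 0.24–0.32 day at 40%. With effective therapy, the adjusted 1.68–1.76 is neither the effect under the treatment actually received (1.52) nor the effect had no one used add-on therapy (2.00).

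**Exclusion instead of adjustment.** In scenario A with d = 0, dropping women who used add-on therapy gives 0.11, 0.14 and 0.12 day at r = 0.3, 0.5 and 0.7. That is the same bias as adjusting, because it selects on the same response.

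**The case against.** The strongest defence is that the section does not commit to this adjustment. The model it fixes is regression on baseline values. The confounders are only potentially relevant, and the two listed beside hormonal therapy can both be baseline variables. A baseline reading of hormonal therapy is possible, and the final covariate set is commonly left to an analysis plan that is not shown. This stands as a reason for low severity. It does not remove the point, because the word additional, as the protocol uses it elsewhere, points to treatment after randomisation, and a candidate named wrongly here can be carried into that plan.

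A second defence is size: every driver of the illustration is assumed, and scenario A, with therapy in resected women only, runs against the authors' own expectation. That is fair. Scenario B follows their expectation and gives a bias in the other direction. Background reports that hormones often do not help but doubts the studies behind this, so neither d = 0 nor d = 2 can be preferred. When therapy works, adjustment recovers part of the dilution.

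A reader might go further and infer from "The control group will receive no additional intervention during the first six months after randomisation" that resected women are free to start add-on therapy while controls are not. The documents do not support this. The sentence mainly defines the comparator, and the later one, "Six months after randomisation all types of additional therapies are allowed", is not limited to an arm and implies a general restriction until then. A missing matching sentence for the resection arm is a detail that a condensed article may leave out.

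A reader might also infer that therapy is allowed during the primary cycle, since "The primary outcome is the number of days with postmenstrual spotting during one menstrual cycle 6 months after randomisation" does not say whether that cycle starts or ends at month 6. The analysis speaks of "The difference between the two groups at 6 months follow-up regarding total number of postmenstrual spotting days during one menstrual cycle", which leans towards data gathered by then, and any relaxation would apply to both arms alike.

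**Conclusion.** The point holds as a minor one. Naming additional hormonal therapy as a confounder is at odds with the protocol's treatment of additional therapy as something given after randomisation, counted as an outcome and expected to respond to resection. Adjusting the month-6 comparison for it can bias the randomised contrast in either direction.

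The size cannot be estimated from the documents and may be zero. Under the stated assumptions with inert therapy, at correlations of 0.3 to 0.7, it is about 0.1 day at 10% uptake (5–7% of the 2-day relevant difference) and about 0.2 to 0.3 day at 40% control uptake (12–16%). These are illustrations and not bounds.

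It does not follow that the primary analysis is already biased, since the adjustment is not firmly planned, nor that the arms are held to different co-treatment rules.

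**What to change.** In Statistical analysis, replace *additional hormonal therapy* with *hormonal therapy in use at baseline*. Add that the intention-to-treat model contains baseline covariates only, and that women who receive add-on therapy are analysed as observed, in the arm to which they were allocated (treatment policy).

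The planned per-protocol analysis can stay. If it excludes women who used add-on therapy, it should not be presented as free of this bias.

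The cost is a wording change of one or two sentences. Sample size, data collection and patient care stay as they are, and the planned registration of add-on therapy in both arms already allows uptake to be reported by arm. What is given up is the partial recovery of a diluted effect where add-on therapy works. No ban on new therapy is needed. It would change patient care and make the secondary outcome on additional therapies less informative.

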### Outcome measures

The primary outcome is the number of days with postmenstrual spotting during one menstrual cycle 6 months after randomisation.

Secondary outcomes are the menstrual characteristics, menstrual related pain and experienced discomfort of both spotting and menstrual pain on VAS of 0–10), quality of life (SF-36, EuroQoL5D, patient satisfaction (5 point scale), sexual function (FSFI), micturition frequency, and urinary incontinence, absence from work (HLQ: Health and Labour [33]), medical consultation, medication use and received additional therapies (diary) at 3 and 6 months after randomisation.

#### Sample size

Based on a systematic review of the literature executed in 2011 we identified one relevant manuscript reporting on a reduction in postmenstrual abnormal uterine bloodloss (PAUB) with an estimated median reduction of 3.8 days after a hysteroscopic niche resection compared to baseline [27]. At baseline, included patients had mean spotting of 7.5 days with a standard deviation of 2.7. Estimated postmenstrual spotting reduced from 7.5 to 3.7 days (see box and whisker plots). Given the fact that the ranges at baseline and after therapy were more or less similar we estimated the SD to be approximately 2.7. However given the lack of a control group without treatment it cannot be excluded that regression to the mean have played a role and may have induced an overestimation of the effect. Given these uncertainties we decided to base our sample size on the difference in postmenstrual spotting days that were considered to be clinically relevant and this should be lower than the previously reported difference of 3.8 in order to prevent insufficient power. Based on experience and confirmed in a survey among patients (unpublished), we considered 2 days to be clinically relevant and a dropout rate of 20 % to be realistic and used these parameters to calculate a sample size to achieve a power of 90 %.

In summary, assuming a difference of postmenstrual spotting of 2 days to be clinical relevant with an estimated SD of 2.7, a dropout rate of 20 %, we need to include 50 patients in each arm to achieve a power of 90 %.

#### Statistical analysis

Analyses will be performed according to intention-to-treat principle and additionally by per protocol analysis. All tests will be performed two sided and a *p*-value <0.05 will be considered as statistically significant. The difference between the two groups at 6 months follow-up regarding total number of postmenstrual spotting days during one menstrual cycle, duration of menstrual bleeding, number of days of brownish discharge, menstrual pain, experienced discomfort of spotting and of menstrual pain, SF-36 domain scores and EuroQol will be analysed using linear regression analyses, adjusted for relevant baseline values. Potentially relevant confounders are additional hormonal therapy, smoking and use of anticoagulation. Logistic regression analysis will be used to evaluate the existence of (midcycle) intra-uterine fluid. To compare satisfaction with treatment, reported on a 0–5 point scale at six months a (multinominal) logistic regression analysis will be used.

We have planned four subgroup analyses, for:

1) Total days of spotting at the end of the menstruation and intermenstrual spotting >25^th^ centile versus ≤ 25^th^ centile and >75^th^ centile or ≤75^th^ centile at baseline;

2) Number of days postmenstrual spotting >25^th^ centile versus ≤2 25^th^ centile and >75^th^ centile versus ≤75^th^ centile at baseline;

3) Small versus larger niches (using a cut-off of residual myometrium of 3 and 5 mm and <50 % of total myometrial thickness (sum of RM and niche depth) at baseline;

4) A history of 1 versus more than 1 CS at baseline.

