### Procedures, recruitment, randomisation, collection of baseline data

Before study entry, the niche will be measured with transvaginal sonography and saline or gel infusion sonography in the sagittal plane where the largest niche is visible and in the transversal plane where the niche is largest i.e. with the thinnest residual myometrium. Depth, residual myometrium and the shape of the niche will be registered (see Fig. 3a, b and c). For inclusion, a niche needs to be at least 2 mm deep and the residual myometrium should not be less than 3 mm in one of the planes during SIS or GIS, given the anticipated risk on perforation or bladder injuries with a smaller residual myometrium. Position of the uterus, fluid in the uterine cavity and/or niche, abnormalities of the fallopian tubes and/or ovaries are also registered. A cervical PAP-smear will be obtained to ensure the absence of cervical dysplasia.

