At the time of randomisation, baseline, obstetric and medical history are reported in the case report file. The patient will receive digital online secured questionnaires at baseline, 3 and 6 months after randomisation about their menstrual pattern and uterine bleeding, will complete a validated menstrual bleeding score chart [28], validated questions to report on quality of life (SF-36: Short Form 36 [29, 30] and Euro-QOL 5D: Euro Quality of Life in 5 dimensions [31]), sexual function (FSFI: Female Sexual Function Index) [32] and absence from work (HLQ: Health and Labour [33]). Medical consultation, medication use and received additional therapies will be registered at the same timepoints in an online diary. Any received additional therapy will be registered in the case report file.

Three months after randomisation all patients will undergo transvaginal sonography to register all niche features as at baseline. Patients will be motivated to undergo a SIS or GIS, however saline or gel instillation will be omitted in case patients experienced too much discomfort during this procedure at baseline (see Fig. 4 for the flowchart).

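### The logistic model for intra-uterine fluid is stated without the baseline adjustment given to the linear models, although fluid is recorded at baseline; adding it is a free, minor gain in precision

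*Protocol article*

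**What the plan says.** All of this is in the protocol article.

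- **Statistical analysis, continuous outcomes.** Spotting days, bleeding duration, discharge, pain, discomfort, SF-36 domains and EuroQol "will be analysed using linear regression analyses, adjusted for relevant baseline values".
- **Statistical analysis, covariates.** The next sentence reads "Potentially relevant confounders are additional hormonal therapy, smoking and use of anticoagulation". It is not tied to one type of model, and it does not name baseline fluid.
- **Statistical analysis, fluid.** "Logistic regression analysis will be used to evaluate the existence of (midcycle) intra-uterine fluid". No covariate and no time point is given.
- **Procedures, recruitment, randomisation, collection of baseline data.** At the scan before study entry, "Position of the uterus, fluid in the uterine cavity and/or niche, abnormalities of the fallopian tubes and/or ovaries are also registered". The phase of the cycle is not stated. The same section provides the follow-up scan: "Three months after randomisation all patients will undergo transvaginal sonography to register all niche features as at baseline". Randomisation is stratified by centre only.
- **Outcome measures.** Intra-uterine fluid is in neither the primary nor the secondary list, so the Statistical analysis section is the only place in the article that describes how it will be compared.

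**The concern.** One paragraph fixes baseline adjustment for the linear models and then states the fluid model without it. An analyst who follows the text literally would fit treatment alone, although each woman's baseline fluid status is on file.

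The stake is precision on one measure. Fluid is the only effect measure given a model in that section that the patient does not report herself. The article's Strengths and limitations section concedes that patients are not blinded and that this could affect what they report. Fluid also bears on the mechanism proposed in the Background, namely retention or accumulation of blood or fluid in the niche or cavity. With a trial of this size, a useful covariate that has already been collected is worth using.

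**Working it through.** **1. Number of women available.** The Sample size section assumes a 2-day difference, an SD of 2.7, 90% power and 20% dropout; the Statistical analysis section sets a two-sided 5% level.

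- n per arm = 2 × (1.960 + 1.282)² × 2.7² / 2² = 38.3, rounded up to 39.
- Allowing for dropout: 39 / 0.80 = 48.75, rounded up to 49. The plan states 50, so its figure reproduces.
- 50 × 0.80 = 40 evaluable women per arm. This is used below, with 45 per arm as a more favourable case.

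This calculation concerns the primary outcome. The article gives no rate, effect or power for fluid, so every fluid rate below is an assumption.

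**2. Power with and without baseline fluid, by correlation.** 3,000 trials were simulated per setting with 40 women per arm. Treatment was tested by likelihood ratio in a logistic model, with and without baseline fluid. Baseline prevalence equals the control follow-up rate. Phi is the within-arm correlation between baseline and follow-up fluid.

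| Follow-up fluid, control vs treated | phi | Power without | Power with | Change (points) |
|---|---|---|---|---|
| 50% vs 25% | 0 | 67.3% | 67.1% | −0.2 |
| | 0.2 | 65.1% | 66.6% | +1.5 |
| | 0.3 | 64.6% | 68.7% | +4.1 |
| | 0.5 | 64.6% | 78.6% | +14.0 |
| 40% vs 15% | 0 | 74.5% | 73.8% | −0.7 |
| | 0.2 | 71.9% | 73.5% | +1.6 |
| | 0.3 | 74.5% | 78.2% | +3.7 |
| | 0.5 | 73.1% | 85.1% | +12.0 |
| 60% vs 30% | 0 | 79.8% | 78.9% | −0.9 |
| | 0.2 | 79.6% | 79.8% | +0.2 |
| | 0.3 | 80.1% | 82.8% | +2.7 |
| | 0.5 | 80.4% | 89.5% | +9.1 |

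With no treatment effect (50% vs 50%), the rejection rate was 5.4 to 5.8% without and 5.4 to 5.6% with baseline fluid.

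**3. Stronger correlation.** A second set of simulations used a treatment odds ratio of 0.25 and follow-up fluid in 60 to 80% of controls with baseline fluid and 15 to 20% of those without. The implied correlation among controls is phi = (rate with − rate without) × √[p(1 − p) / (q(1 − q))], where p is baseline prevalence and q is overall follow-up prevalence.

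- Rates 60% and 20%, p = 0.40: q = 0.36 and phi = 0.40 × √(0.24 / 0.2304) = 0.41. With 45 per arm, power goes from 68.9% to 73.3% (+4.4 points).
- Rates 80% and 15%, p = 0.50: q = 0.475 and phi = 0.65 × √(0.25 / 0.2494) = 0.65. With 45 per arm, power goes from 54.1% to 73.3% (+19.2 points). With 40 per arm, it goes from 48.6% to 66.8% (+18.2 points).

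**4. Chance imbalance.** Take p = 0.40, 45 per arm, and control follow-up rates of 70% and 15%, a gap of 55 points. With an odds ratio of 0.25 the treated rates are 36.8% and 4.2%, a gap of 32.6 points.

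- SD of the between-arm difference in baseline prevalence: √(2 × 0.4 × 0.6 / 45) = 10.3 points.
- Part of the unadjusted follow-up difference that this carries: √[(0.24 / 45) × (0.55² + 0.326²)] = 4.7 points.
- Total standard error of the unadjusted difference, with overall rates of 37.0% and 17.3%: √[(0.370 × 0.630 + 0.173 × 0.827) / 45] = 9.1 points.

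The 4.7 points are already part of the 9.1. Adjustment removes variance that the unadjusted test has correctly allowed for.

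**The case against.** The strongest reply is that the text is silent on covariates and does not choose an unadjusted model. It names a suitable model for a binary outcome, nothing in it rules out adjustment, and the confounder sentence just before it is not confined to the linear models. The article condenses a fuller protocol, and a covariate list for a measure outside the listed outcomes could well sit in an analysis plan that is not shown. The outcome is labelled midcycle while the cycle phase of the baseline scan is unstated, so the two may be only weakly related.

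Much of this stands. It keeps the point minor and makes the size of the gain conditional. It does not remove the point, because the paragraph does specify baseline adjustment for one group of models and leaves it out for the next. A covariate that costs nothing when uninformative and helps when informative improves on the model as stated.

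Two stronger readings are tempting. A reader might infer that the unadjusted analysis necessarily loses power; that does not follow, because the document gives no correlation and the loss is nil at phi 0. A reader might also infer that chance imbalance in baseline fluid biases the comparison. It does not: randomisation removes bias on average, and type I error is near 5% both ways. What adjustment offers is precision and an estimate that takes account of the imbalance actually seen.

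**Conclusion.** The point holds as a minor improvement to the stated analysis. Read as written, the fluid model omits a baseline covariate that the trial collects and that the neighbouring linear models would include. The expected gain in power is about 0 points with no correlation, 0 to 2 at phi 0.2, 3 to 4 at phi 0.3 and 9 to 14 at phi 0.5, rising to about 19 at phi near 0.65. These figures rest on assumed fluid rates, treatment effects and correlations with 40 to 45 women per arm; the article supplies only the sample size and dropout. The primary outcome, its analysis and the 50 per arm are unaffected.

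**What to change.** Add a clause to the fluid sentence in the Statistical analysis section so that the logistic model includes presence of fluid at the baseline scan as a covariate, in line with the linear models. If an analysis plan already says so, carry its wording across. Fixing this before the data are seen also rules out a later choice between adjusted and unadjusted results. Reporting a standardised risk difference beside the odds ratio would help readers but is optional.

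The cost is one clause of text, with no new data and no change to the sample size.

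### Patient satisfaction is an ordered secondary outcome, but the logistic model named for it ignores the ordering, and the protocol describes the scale in two ways

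*Protocol article*

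**What the plan says.** Outcome measures in the protocol article lists "patient satisfaction (5 point scale") among the secondary outcomes. Statistical analysis returns to it: "To compare satisfaction with treatment, reported on a 0–5 point scale at six months", followed by "a (multinominal) logistic regression analysis will be used". No ordinal or rank method is named for this outcome. The general rules are "All tests will be performed two sided" and a p-"value <0.05 will be considered as statistically significant".

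The article gives no power or sample size for satisfaction. The only sizing is for spotting days, under Sample size: "we need to include 50 patients in each arm to achieve a power of 90"%, with "a dropout rate of 20"% included.

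**The concern.** There are two separate issues.

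- **Model.** The levels of a satisfaction score have a natural order. A multinomial model does not use it. It estimates one treatment coefficient for each level other than the reference, so an upward shift in satisfaction is split over several odds ratios and tested on several degrees of freedom. With a trial of this size, some level may also be empty in one arm, and the odds ratio for that level is then zero or infinite.
- **Scale.** Five points (for example 1 to 5) and 0–5 are not the same scale. Read literally, 0–5 has six integer levels. The number of levels determines the questionnaire item and the number of parameters in the model, and nothing in the article reconciles the two descriptions.

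At stake is how well the trial can detect and summarise a difference in satisfaction. The primary result is not at stake.

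**Working it through.** **1. Number of women available.** The inputs are in Sample size: difference 2 days, SD 2.7, power 90%, dropout 20%. Two-sided 5% comes from Statistical analysis.

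n = 2 × (1.960 + 1.282)² × (2.7/2)² = 2 × 10.51 × 1.8225 = 38.3, so 39 per arm. Then 39/0.8 = 48.75, so 49. The t-test version gives 39.3/0.8 = 49.1, so 50. The stated 50 per arm reproduces. After 20% dropout, 50 × 0.8 = 40 per arm are evaluable. That is the n used below.

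**2. Treatment parameters.** With K levels, a multinomial model has K − 1: four for five levels, five for six. A proportional-odds model has one.

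**3. Cost of the extra degrees of freedom.** Suppose the whole effect lies in the ordered direction. A 1-df test with power P has noncentrality (1.960 + z_P)². The same noncentrality is then referred to the chi-square critical value for 4 df (9.49) or 5 df (11.07).

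| Ordinal test, 1 df | Noncentrality | Multinomial, 4 df | Multinomial, 5 df |
|---|---|---|---|
| 80% | 7.85 | 59.5% | 55.5% |
| 90% | 10.51 | 74.0% | 70.3% |

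**4. Simulation at 40 per arm.** The category distributions and odds ratios are assumptions, because the article gives none. Cumulative odds in the second arm are shifted by a common odds ratio. The multinomial test is the likelihood-ratio statistic 2 Σ O log(O/E) on K − 1 df. The ordinal test is the tie-corrected rank test, which is the score test of the proportional-odds model. At a common odds ratio of 2.5, over uniform, peaked and skewed scales:

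| Analysis | Treatment parameters | Power |
|---|---|---|
| Multinomial | 4 or 5 | about 41–43% |
| Binary, top two levels against the rest | 1 | 42–55% |
| Ordinal rank test | 1 | 59–62% |

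Some assumed distributions move the first and third rows up by about a point (to 44% and 63%). The loss from the multinomial model is thus about 59 − 43 = 16 to 62 − 41 = 21 points. For the binary split it runs from about 62 − 55 = 7 points (uniform scale) to 59 − 42 = 17 points (skewed scale).

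At odds ratios 2, 3 and 4 the multinomial test has 26–27%, 55–59% and 78–80%, against 40–42%, 77–78% and 92–93% for the rank test. With no effect, the multinomial test rejects in 5.7–6.5% of trials and the rank test in 4.8–5.2%.

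**5. Empty cells, five levels, odds ratio 2.5.** A cell with probability p is empty in an arm of 40 with probability (1 − p)⁴⁰.

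- Uniform scale: the lowest level in the shifted arm has odds 0.25/2.5 = 0.10, so p = 0.091 and 0.909⁴⁰ = 0.022. With the small contributions of the other cells, the total is about 3%.
- Peaked symmetric scales: 8% (15/20/30/20/15) and 21% (10/20/40/20/10).
- Scale skewed towards satisfied, for example 5/10/20/35/30: the lowest level alone gives 0.95⁴⁰ = 0.13 in one arm and (1 − 0.0206)⁴⁰ = 0.43 in the other. With the remaining cells, the total is about 60%.

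**The case against.** The strongest point against is the wording. The qualifier is in parentheses, so the sentence may mean logistic regression, multinomial only if more than two categories are kept. This stands: a reader might infer that the plan commits to a multinomial model, and the text does not fix that. It does not remove the concern, because a binary analysis also discards ordering. It does narrow the loss, to about 7–9 points on symmetric scales. That no cut-point is given is not a fault in itself, since a condensed article may leave that to an analysis plan that is not shown.

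Secondly, a reader might infer that the planned analysis will probably miss a real shift or give unusable estimates. The figures do not support that as a general statement. At odds ratio 3 the multinomial test still detects the shift in 55–59% of trials. An empty cell spoils the odds ratio for one level, but the overall likelihood-ratio test can still be computed. How often it happens depends almost entirely on a distribution that the article does not give.

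Thirdly, a reader might take satisfaction to be a key outcome. The article lists it without emphasis among many secondary outcomes and claims no power for it.

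Fourthly, the simulated shift is exactly proportional-odds, which favours the ordinal test. This also stands. With a non-monotone effect the multinomial model could do better, although a directional shift is the more plausible one for satisfaction.

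Finally, the two scale descriptions may be loose wording for one instrument. That is possible, and the power result is nearly the same either way, but the text needs to say which.

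**Conclusion.** The point holds as a minor one. For an ordered secondary outcome the article names a logistic model that, in its multinomial or its binary reading, does not use the ordering, and it describes the scale inconsistently. If the true difference is an ordered shift, the multinomial version costs about 16–21 points of power at a common odds ratio of 2.5 with 40 women per arm, and it gives no single treatment effect. These sizes rest on assumed category distributions, on proportional odds and on the planned 20% dropout. The spotting-days analysis and the 50 per arm are not affected.

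**What to change.** - State one satisfaction scale, with its levels and their labels, identically under Outcome measures and Statistical analysis.
- Replace the logistic model for this outcome by a proportional-odds (ordinal) logistic model that reports one common odds ratio with its confidence interval, and name a rank test as a check.
- Account for centre only if the number of centres allows it, for example by a stratified rank test. The article does not state how many centres take part, and centre terms with about 80 evaluable women could bring sparse-data problems of their own. The figures above include no centre term.

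This changes wording only and needs no additional patients, visits or data. The price is reliance on the proportional-odds assumption, and lower power than the multinomial model if the effect is not monotone over the scale.
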